# Effect of strength-based physical exercise on telomere length as a marker of premature ageing in patients with schizophrenia: study protocol for a pilot randomised controlled trial

**DOI:** 10.1192/bjo.2024.753

**Published:** 2024-09-26

**Keywords:** Ageing, exercise, mortality, schizophrenia, telomere

## Abstract

**Background:**

Patients with schizophrenia die decades earlier than the general population. Among the factors involved in this mortality gap, evidence suggests a telomere length shortening in this clinical population, which is associated with premature ageing. Recent studies support the use of strength-based training exercise programmes to maintain, or even elongate, telomere length in healthy elderly populations. However, studies aiming at modifying telomere length in severe mental illnesses, such as schizophrenia, are still very scarce.

**Aims:**

To investigate the effect of a strength-based physical exercise programme on the telomere length of individuals with schizophrenia.

**Method:**

We propose a pragmatic, randomised controlled trial including 40 patients aged ≥18 years, with a stable diagnosis of schizophrenia, attending the Complejo de Rehabilitación Psicosocial (CRPS, Psychosocial Rehabilitation Centre) in Salamanca, Spain. These patients will be randomly assigned (1:1) to either receive the usual treatment and rehabilitation programmes offered by CRPS (treatment-as-usual group) or these plus twice weekly sessions of an evidence-based, strength-based training exercise programme for 12 weeks (intervention group). The primary outcome will be effect on telomere length. Secondary outcomes will include impact on cognitive function, frailty and quality of life.

**Results:**

We expect to show the importance of implementing strength-based physical exercise programmes for patients with schizophrenia. We could find that such programmes induce biological and genetic changes that may lengthen life expectancy and decrease physical fragility.

**Conclusions:**

We anticipate that our trial findings could contribute to parity of esteem for mental health, reducing premature ageing in patients with severe mental illnesses, such as schizophrenia.

Schizophrenia can have a significant impact not only on mental health, but also on physical well-being.^1–3^ This chronic and debilitating mental disorder is characterised by a blend of hallucinations, delusions, disorganised thoughts, erratic behaviour and negative symptoms such as poverty of speech, lack of motivation or loss of interest in enjoyable activities.^4^ Individuals with schizophrenia experience a higher incidence of physical health problems compared with the general population. This may be attributed to the side-effects of antipsychotic medications, insufficient physical activity and a higher prevalence of unhealthy lifestyle habits such as smoking, illicit drug use and alcohol consumption.^5^ Several studies have shown that people with schizophrenia have a significantly shorter life expectancy than the general population, largely because of higher premature mortality rates.^6,7^ An observational study published in 2017 found that the standardised mortality rate in individuals with schizophrenia was more than twice that of the general population, with an even higher risk for those with early-onset schizophrenia.^8^

This premature mortality could also be linked to accelerated telomere shortening. Telomeres are protective structures at the ends of chromosomes that shorten with each cell division.^9^ Telomere length is associated with cellular ageing and health deterioration. Multiple studies have established that populations with shorter telomeres have an increased risk of chronic diseases and higher mortality rates.^10–12^ Telomere shortening has been related to different factors, including genetic causes. For instance, certain gene polymorphisms involved in the expression of telomerase, an enzyme responsible for maintaining and elongating telomeres, can have an impact on its function and, consequently, on telomere length. In fact, functional single nucleotide polymorphisms (SNPs) in the *TERT* gene can affect telomerase expression and activity, as shown in a meta-analysis conducted by Liu et al.^13^ In addition, SNPs in the loci encoding *TERT* and *TERC* genes are associated with telomere length and also an increased risk of age-related diseases and mortality.^14–17^

A recent systematic review with meta-analysis revealed that people with an established diagnosis of schizophrenia, typically more than 5 years from its onset, had shorter telomeres compared with individuals without mental disorders, indicating premature cellular ageing.^18^ These findings highlight the importance of identifying organic risk factors in vulnerable individuals with schizophrenia, and improving access to long-term physical care and monitoring to prevent premature mortality. Furthermore, these results also suggest that interventions to delay or prevent telomere shortening may be beneficial for those diagnosed with schizophrenia.

One of the non-pharmacological treatments that has demonstrated a positive impact on the physical and mental well-being of individuals with schizophrenia is physical exercise.^19^ Firth et al conducted a systematic review investigating the effects of physical exercise on the mental and physical health of individuals with schizophrenia. They found that physical exercise can ameliorate symptoms of the illness, enhancing quality of life and improving physical functioning.^20^ Many scientific contributions advocate for physical exercise as a first-line non-pharmacological treatment to address physical and cognitive impairments in people with schizophrenia.^20–22^ On the other hand, recent studies have shown that strength-based training exercise has beneficial effects on the telomere length of elderly populations.^23^

However, despite all this evidence, there is no interventional study assessing the impact of physical exercise, specifically strength-based, on telomere length in individuals with schizophrenia, who exhibit shorter telomeres.

## Main and secondary objectives

The main objective of this study will be to investigate the effect of strength-based physical exercise on telomere length in individuals diagnosed with schizophrenia. The secondary objectives will be to:
explore the impact of physical exercise and telomere length on cognition;examine the influence of physical exercise and telomere length on frailty;assess the effect of physical exercise and telomere length on the quality of life;determine potential correlations between physical parameters related to frailty and telomere length;establish the importance of telomerase (enzyme involved in telomere length maintenance) gene polymorphisms.

## Method

We propose a pragmatic, randomised controlled trial, where we shall test the effect of a 12-week strength-based training exercise programme on the telomere length of individuals with schizophrenia. The trial follows the Consolidated Standards of Reporting Trials (CONSORT) Statement^24^ and the treatment protocol is described in accordance with the recommendations of the Standard Protocol Items: Recommendations for Interventional Trials (SPIRIT).^25^ The study will be conducted from 1 January 2024 to 1 September 2024.

The authors assert that all procedures contributing to this work comply with the ethical standards of the relevant national and institutional committees on human experimentation and with the Helsinki Declaration of 1975, as revised in 2008. All procedures involving human patients were approved by the Research Ethics Committee at the Salamanca University Healthcare Complex on July 2023 (reference 2023/07). The trial is registered with Clinicaltrials.gov (registration number NCT05978921).

All patients in the study will be informed about the objective of the study and will give their written informed consent to participate in the study. The patients’ right to privacy will be respected, the applicable data protection laws in force will be observed and the anonymity of all study participants will be guaranteed when data are presented in scientific journals. Patients’ medical data will be considered confidential, and disclosure to third parties will be forbidden. To ensure proper confidentiality, identification numbers will be randomly assigned to each participant. The intervention sessions will be adapted to each patient, making those modifications in the intervention that are necessary to maintain patient's safety. The risk of therapy-related adverse events is minimal. However, if (serious) adverse events should occur during or after the study, these will be monitored by the study team and physicians as part of standard therapy. All serious adverse events will be documented and reported immediately (within a maximum of 24 h) to the principal investigators of the study.

### Study participants and setting

Participation in the study will be voluntary, and potential participants will be provided with explanations of the study objectives and methodology before completing and signing an informed consent form.

#### Inclusion criteria

Inclusion criteria are patients with an established DSM-5-TR diagnosis of schizophrenia for at least 5 years, who are attending the Complejo de Rehabilitación Psicosocial ((CRPS) Psychosocial Rehabilitation Centre) or its associated out-patient clinic for severe mental disorders in Salamanca, Spain. The CRPS is an out-patient rehabilitation centre that, in addition to pharmacological treatment and follow-up by mental health professionals, offers a series of rehabilitation programmes in the community, including psychosocial interventions, social reinsertion, employment advocacy and support, and family interventions, among others.

#### Exclusion criteria

Exclusion criteria are patients without mental capacity to understand the study information sheet or to sign the informed consent. Also, those who would be unable to engage in a physical training of a moderate intensity because of medical reasons will be excluded from the study.

### Study intervention

Participants will be randomly assigned to either the intervention or treatment-as-usual groups.

Participants in the intervention group will have access to the usual treatment programmes at CRPS, but will also enrol into twice weekly 50 min sessions of strength-based physical exercise over 12 weeks. Patients in the treatment-as-usual group will continue accessing the traditional CRPS programmes, but will not participate in the strength-based exercise sessions.

The exercise sessions will be carried out at the ‘Contemporánea’ Physiotherapy Clinic in Salamanca (https://www.fisiocontemporanea.com/).

In accordance with previous studies involving moderate exercise training programmes for patients with schizophrenia, the duration of the intervention will be limited to 12 weeks.^26,27^ The training sessions will follow an evidence-based physical activity programme with successful outcomes on telomere length in healthy populations,^23^ and will be structured as follows:
Part 1: Warm-up with an aerobic component lasting approximately 15 min.Part 2: Twelve multi-analytical exercises based on the strength endurance component. Six of these exercises will be performed during the first weekly session, and the rest during the second. Each exercise will comprise three sets of 12 repetitions. The proposed exercises are as follows:
First session: squat and row with band; glute bridge and kettlebell chest press; backward lunge and abdominal pull-off with band; push up; glute kickback with band; abdominal crunch.Second session: wall ball squat; step up and kettlebell overhead press; abdominal pull-off and lateral split squat with slider; pullover with band; kettlebell deadlift; kettlebell split squat.Part 3: Cool-down phase with breathing and stretching exercises.Before the intervention begins, participants will undergo two to three preparation sessions, in which they will practice the exercises that they will later carry out over the 12 weeks.

These sessions will also help tailor the exercise load for each individual. Participants will be introduced to the Rating Scale of Perceived Exertion (RPE),^28^ based on the number of repetitions in reserve (RIR).^29,30^ Participants will be encouraged to perceive an effort level between 7 and 8 on the RPE scale^28^ (0–10; 0 being no effort at all and 10 being maximal effort) during each exercise. If participants consistently complete 12 repetitions with lower perceived exertion than specified in two consecutive sessions, the training load will be increased by approximately 2–10%, following the guidelines of the American College of Sports Medicine.^31^ The RIR-based RPE will be re-evaluated.

### Patient and public involvement

Patients have been involved in the design and will participate in the delivery of this trial. For instance, patients with schizophrenia currently attending the CRPS were consulted on the feasibility of running this project and some of them were involved in its design, specifically on where and how to carry out the training sessions. In addition, two CRPS staff members, with lived experience of severe mental illness, may support physiotherapists at the ‘Contemporánea’ Physiotherapy Clinic in delivering physical training sessions (the intervention).

### Variable and outcomes: type and measurement

#### Primary variable and outcome

##### Telomere length

Telomere length will be calculated using a protocol similar to other studies.^23^ DNA will be extracted from saliva following a specific protocol.^32,33^ Cells will be isolated through centrifugation and resuspended in Fornace buffer. The resulting pellet will undergo incubation for protein degradation and cell membrane breakdown. Subsequently, DNA will be extracted, purified using the phenol-chloroform method and precipitated with cold absolute ethanol.

The concentration of the extracted DNA will be determined by measuring absorbance at 260 nm, using a NanoDrop 2000/2001 spectrophotometer. DNA purity will be assessed based on the A260/280 absorbance ratio, with an optimal ratio ranging from 1.8 to 2.0. Extracted DNA samples will be stored in Eppendorf tubes at −20 °C.

Telomere length in saliva cells from each participant will be measured with quantitative real-time polymerase chain reaction in conjunction with the Absolute Human Telomere Length Quantification qPCR Assay Kit (ScienCell, Catalog #8918, California, USA). This technique quantifies the initial amount of DNA coding for telomerase (TEL) and compares it with that from another fragment corresponding to a single-copy reference gene (SCR) for endogenous control. The difference in the amount of DNA quantified represents each participant's relative telomere length. A reference fragment (CONTROL) with a known telomere length, provided by the manufacturer, will be added to each assay, to allow absolute quantification of telomere length in each sample.

The reactions will occur in a Micro-Amp Fast Optical 96-Well reaction plate (Applied Biosystems), using the Applied Biosystems StepOnePlus Real-Time PCR System. Triplicate reactions will be performed for each sample, to minimise variability. The amplification program will consist of 10 min at 95 °C, followed by 40 cycles at 95 °C for 15 s, 52 °C for 30 s and 60 °C for 1 min.

The Ct (2^−ΔΔCt^) comparative method will be employed to calculate the relative expression levels of each amplicon. The specificity of each polymerase chain reaction will be confirmed by verifying the telomere length of the reference sample (CONTROL), which, in turn, allows determination of absolute lengths for each sample for a diploid cell and/or chromosome end. Data management will be conducted with Microsoft Excel, version 16 for Windows.

#### Secondary variables and outcomes

##### Cognitive function

Cognition will be assessed with the Brief Assessment of Cognition in Schizophrenia (BACS).^34^ The BACS score ranges from 0 to 100 points, with a higher score indicating better cognitive performance within the normative population.

##### Frailty

Frailty will be measured with the Short Physical Performance Battery scale (SPPB),^35^ which comprises three components: a balance test, walking time and standing from a seated position. The maximum score is 12 points, with a higher score indicating better physical functioning.

##### Quality of life

Quality of life will be evaluated with the EuroQuality of Life (EQ-5D-5L scale),^36,37^ which ranges from 0 to 100, with 100 representing the best imaginable health and 0 representing the worst.

In addition to the primary and secondary variables, we shall collect basic sociodemographic information, such as age (years), gender (female), weight (kilograms) and height (centimetres).

### Sample size

Because of the lack of previous interventional studies looking into changes in telomere length following physical exercise in patients with schizophrenia, the sample size calculation was based on a pre–post study, using the proposed intervention in elderly healthy participants.^23^ Accordingly, for an identified Cohen's effect size of 1.1, a statistical power of 90% and an alpha level of 0.05 with a one-sided contrast, we would need a sample size of 32 individuals (16 per group). To account for potential study losses, a 20% lost-to-follow-up rate was considered, leading to a required sample of 40 participants (20 per trial arm). We employed the R Statistical Software pwr package for this calculation (version 4.4.2 for Windows, The R Foundation; https://www.r-project.org/).

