### Data analysis

We shall describe data emerging from the study by using means and s.d., and medians and interquartile ranges for quantitative variables, and percentages for qualitative values. Normality will be assessed with the Kolmogorov–Smirnov test with the Lilliefors correction, and by examining box plots.

For group comparison, we shall employ the *t*-test for independent variables when these follow a normal distribution, and non-parametric Mann–Whitney *U-*test for non-normal distributions. The Levene test will be used to assess population equality variances. To analyse changes over time for unidimensional measurement tools within the trial groups, a two-factor analysis of variance will be used, with one factor being independent variables (intervention and treatment-as-usual group) and the other dependent (pre, post). If the tool has multiple dimensions, a three-factor analysis of variance will be used, with one independent factor (intervention, control) and two dependents (time: pre–post and dimension). In the event that there is missing data, we will use mixed models. We shall also use *post hoc* Bonferroni corrections.

All parameters will be presented with 95% confidence intervals, and statistical significance will be determined when *P*-values are <0.05. Data analyses will be performed with IBM SPSS version 28 for Windows and R statistical software.

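### The 90% power is calculated for a one-sided 5% test, but the analysis section declares no one-sided test and reads as two-sided, for which power at 16 per arm is about 85%

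*Protocol article*

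**What the plan says.** The Sample size section takes its effect size from earlier work: "the sample size calculation was based on a pre–post study, using the proposed intervention in elderly healthy participants". It plans "for an identified Cohen's effect size of 1.1, a statistical power of 90" per cent, with "an alpha level of 0.05 with a one-sided contrast, we would need a sample size of 32 individuals (16 per group"). It then allows for attrition: "a 20% lost-to-follow-up rate was considered, leading to a required sample of 40 participants (20 per trial arm").

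The Data analysis section does not mention a one-sided test. For group comparisons it names the independent-samples t-test, or the Mann–Whitney test if the data are not normal. For change over time it names a two-factor analysis of variance (group by pre/post). It closes with a general rule, "All parameters will be presented with 95% confidence intervals, and statistical significance will be determined when" P-values are below 0.05. It does not use the words one-sided or two-sided.

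**The concern.** Power belongs to a particular test at a particular error rate. The sample size was worked out for a test that spends the whole 5% in the favourable direction. The analysis section reads as a conventional two-sided 5% analysis:

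- A 95% confidence interval excludes zero exactly when the two-sided 5% test is significant. A one-sided 5% test would go with a 90% interval or a one-sided 95% bound.
- The F-test of a group-by-time interaction has no direction. With two groups and two time points it is equivalent to a two-sided t-test on the change scores.
- A 0.05 threshold with no stated direction is ordinarily read as two-sided.

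If the two-sided reading is right, the trial has a larger chance of missing the planned effect than its stated 10%. The decision rule for the primary outcome is also left unsettled, because a reader cannot tell which threshold a positive result has to meet.

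**Working it through.** **Inputs.** All come from the Sample size section: d = 1.1, alpha = 0.05 one-sided, power 90%, 16 evaluable per group, 20% loss, 40 recruited. As the protocol does, d is taken as the standardised difference between the two groups.

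**Method.** Two-sample t-test with n per group: degrees of freedom 2n − 2, noncentrality d × √(n/2). Power is the probability that the noncentral t variable exceeds the critical value (for the two-sided test, in either tail).

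**Step 1: reproduce the plan's figure (one-sided 5%).**
- The exact solution for 90% power is n = 14.9, so 15 per group (power 90.2%).
- At n = 16, the noncentrality is 1.1 × √8 = 3.111 with 30 degrees of freedom. The one-sided critical value is 1.697 and power is 91.9%.
- Attrition: 32 / (1 − 0.20) = 40.

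The stated 16 per group is one more than the minimum and delivers the stated power on its own inputs. The attrition step is exact.

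**Step 2: same design, two-sided 5%.**
- At n = 16, the noncentrality is still 3.111, but the critical value rises to 2.042. Power is 85.3%.
- The shortfall is 90 − 85.3 = 4.7 percentage points. The chance of missing the effect is 14.7% instead of 10%.

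**Step 3: what two-sided 90% power needs.**
- The exact solution is n = 18.4, so 19 per group, or 38 evaluable.
- With 20% loss: 38 / 0.8 = 47.5, so 48 recruited (24 per arm) against the planned 40.
- With 16 per group held fixed, the effect needed for 90% power is d = 1.185, or about 1.19.

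**Step 4: dependence on attrition (d = 1.1, 20 recruited per arm).**

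| Evaluable per arm | Loss | One-sided 5% | Two-sided 5% |
|---|---|---|---|
| 16 | 20% | 91.9% | 85.3% |
| 18 | 10% | 94.4% | 89.4% |
| 19 | 5% | 95.4% | 91.0% |
| 20 | 0% | 96.2% | 92.4% |

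Under a two-sided test, 90% is reached only with 19 or 20 evaluable per arm.

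**Step 5: the rank-test fallback.** If Mann–Whitney is used, and its efficiency relative to the t-test is assumed to be 0.955 (the large-sample value under normality), two-sided power at 16 per group is about 84%.

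**The case against.** Four points can be made against this.

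**The analysis section never says two-sided.** The t-test and Mann–Whitney test can both be run one-sided, and the only statement on direction anywhere in the article is the one-sided contrast in the Sample size section. This stands as a limit: two-sidedness is inferred. It does not remove the inconsistency, because the 95% intervals do not match a one-sided 5% test and nothing in the analysis section declares one.

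**The analysis of variance may not apply to telomere length.** Its wording, about measurement tools with one or several dimensions, fits the cognitive, frailty and quality-of-life scales better, and the section does not say which test is primary. This partly stands, so the F-test argument should not carry the point alone. The 95% interval rule is stated for all parameters and so covers the primary outcome.

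**The shortfall is small, and the trial is titled a pilot.** It is under five points, arises at the full planned loss, and disappears with 19 or 20 evaluable per arm. The effect size matters more: it comes from a pre–post study in healthy elderly people, and at d = 0.8 power with 16 per group would be 71% one-sided and 59% two-sided. This argues for moderate severity. Being a pilot does not excuse the mismatch, because the protocol itself claims 90% power.

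**The calculation is correct.** This stands in full, as Step 1 shows.

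A reader might also infer that the sponsor means to report a one-sided P-value at the end in order to gain significance. The document does not support that. The one-sided contrast is already published in the protocol, and nothing indicates an intention to change tests.

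**Conclusion.** The concern holds as an inconsistency between two sections. The 90% power belongs to a one-sided 5% test, while the analysis as written corresponds to two-sided 5% testing. On that reading, power at the planned 16 evaluable per arm is 85.3%, and 90% requires 19 per arm.

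The figures assume a normally distributed outcome, a two-sample t-test and a true between-group d of 1.1. They also depend on the inferred two-sided primary test: if the sponsor does intend a one-sided test, the stated power is met and the defect lies in the analysis section, which omits the direction and specifies intervals that do not match.

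Two stronger readings should be resisted. It would be wrong to call the sample size miscalculated, since it reproduces on its own inputs. It would also be too strong to say flatly that the trial lacks its stated power, since that depends on an unstated direction and on attrition. Severity is moderate.

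**What to change.** Keep 40 participants and make the two sections agree.

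- In Data analysis, add that the primary test on telomere length is two-sided at the 5% level.
- In Sample size, replace the power statement with: *with 16 evaluable participants per arm and a two-sided 5% test, power is 85% for d = 1.1; 90% power requires d of about 1.19.*

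The equally coherent alternative is to prespecify a one-sided primary test in Data analysis, justify it, and report a matching interval (a one-sided 95% bound or a two-sided 90% interval). The present power statement could then stay.

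Either route costs a sentence or two and needs no extra participants. The first means a slightly less favourable stated power. The second means defending a one-sided test. Holding two-sided power at 90% under 20% loss would instead mean recruiting 48, which is not necessary to resolve the inconsistency.
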